### Data management

Study coordinators will enter data collected into a password-protected database developed for ease of entry and reduction of error. All data will be error-checked and transferred to a statistical modelling software by the biostatistician in the team. Study data will be kept confidential and de-identified, and only authorized study staff will have access.

### Data analysis

We will use the following statistical methods to evaluate the specific aims.

*Aim 1: To evaluate the clinical effectiveness of stepped-care* versus *screening alone:* All analyses will be based on the intention-to-treat (ITT) principle. We will employ a mixed model approach to analyse the primary outcome variable, with repeated measurements taken at the 1-, 3-, 6- and 12-month follow-up visits. These models allow for different number of observations per subject, use all available data on each subject, and are unaffected by randomly missing data. We will examine the fixed categorical effects of treatment pathway (STEP, SCREEN), visit time (1, 3, 6, and 12 months), and treatment pathway-by-visit time interaction. The restricted maximum likelihood approach will be utilized for estimation. Significance tests will be based on least squares means using a two-sided alpha = 0.05. Primary treatment comparisons will be contrasts in least squares means between treatment groups at the endpoint visit. The CGI scores and SCID diagnoses will be analysed in a similar fashion. As a follow-up to the ITT analyses, we will also conduct a completer analysis. Participants in the STEP arm who are stepped up to CBT and complete four out of five of the CBT sessions will be deemed completers. Those in the STEP arm who complete the psychoeducation session and are not stepped-up to CBT will also be considered completers for the purpose of analysis.

*Aim 2: To evaluate the patient-centred effectiveness of stepped-care* versus *screening alone:* We will use the same mixed model approach as outlined under Aim 1 to analyse data from the patient-reported outcomes (SF-12, EQ-5D, and PDSQ).

*Aim 3: To assess the cost-effectiveness of stepped-care* versus *screening alone from the health system perspective:* We will estimate the ICER for the STEP arm participants relative to the SCREEN arm participants at 12 months from baseline. The ICER is calculated as the difference between the costs of the two strategies divided by the difference in their effectiveness. Costs from the health system perspective will be the difference in average costs between those in the STEP and SCREEN arms, based on hospital billing data. The difference in effectiveness will be based on the quality of life weights generated by applying the SF-6D algorithm to scores from the SF-12 survey. The STEP intervention will be considered dominant over SCREEN if it incurs less costs and generates higher quality-adjusted life years (QALYs). STEP will be considered cost effective relative to SCREEN if the ICER is below the cost-effectiveness threshold. We will adopt the National Institute for Health and Care Excellence’s cost-effectiveness threshold of £20,000–30,000 per QALY gained, which roughly translates into $63,313 SGD per QALY gained [51].

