### Specific aims

*Aim 1 (Primary):* To evaluate the clinical effectiveness of a stepped-care intervention for ED patients with panic-related anxiety compared to screening alone.

*Outcomes under Aim 1:* The primary outcome under Aim 1 will be clinician-rated severity of panic symptoms, measured using the Panic Disorder Severity Scale (PDSS) [30] and the Clinical Global Impression Scale (CGI) [31]. Panic disorder will be diagnosed using the Structured Clinical Interview for DSM-5 (SCID) [32].

*Aim 2:* To evaluate the patient-centred effectiveness of a stepped-care intervention for ED patients with panic-related anxiety compared to screening alone.

*Outcomes under Aim 2:* We will examine health-related quality of life using the 12-item Short Form Health Survey (SF-12) [33], and the EuroQoL–5 Dimension (EQ-5D) [34]. We will assess psychiatric comorbidity using the Psychiatric Diagnostic Screening Questionnaire (PDSQ) [35], and healthcare utilization for panic-related symptoms (ED visits and hospital admissions) based on electronic medical record data in the 12 months following the intervention.

*Aim 3:* To evaluate the incremental cost-effectiveness of a stepped-care intervention for ED patients with panic-related anxiety compared to screening alone, from the health system perspective.

*Outcomes under Aim 3:* We will calculate the incremental cost-effectiveness ratio (ICER) of stepped-care intervention relative to screening alone, at 12 months from baseline. Direct healthcare costs will be calculated from electronic billing records and the effectiveness of the intervention will be assessed based on the conversion of SF-12 form to a quality of life weight using the Short Form Health Survey 6D (SF-6D) algorithm [36].

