### Sample size

We will aim to recruit a randomized sample of 212 participants. Sample size was estimated based on change in panic symptom severity with PDSS score at 1-month post-intervention as the primary outcome. Previous studies of the 5-session CBT protocol for patients with panic disorder showed relatively large effect size changes on the PDSS from pre- to post-intervention [42] (Cohen’s d = 2.03–2.62). Based on previous literature, we expect a more modest effect size change for the psychoeducation intervention alone [24]. Assuming the true difference between treatments to be 0.516 times the common standard deviation (i.e., Cohen’s d = 0.516, which is approximately Cohen’s medium effect size), a final sample size of 80 participants in each group (after accounting for 25% attrition) would ensure 90% power at a two-sided 0.05 significance level.

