### Randomization

Patients will be randomly allocated to one of the two arms based on a code generated using the open-source software R (https://www.r-project.org) and contained within sequential sealed envelopes. We will stratify the participants by the diagnosis of panic attack or panic disorder. Within each stratum, we will apply a permuted block randomization scheme with a block size of 4 and a 1:1 randomization ratio between the screening alone (SCREEN) or stepped-care intervention (STEP) arms. This permuted block randomization will ensure balance in the trial. The randomization block will be generated before commencing the study at the various sites. The study coordinator will proceed to open the randomisation envelopes to reveal the allocation only after a patient has been enrolled in the trial.

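### The primary mixed model names neither baseline PDSS nor the randomisation stratum, so it gives up precision and makes the test conservative

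*Protocol article*

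**What the plan says.** Under Aim 1 in Data analysis, the protocol article plans a mixed model on "repeated measurements taken at the 1-, 3-, 6- and 12-month follow-up visits". Its terms are the "fixed categorical effects of treatment pathway (STEP, SCREEN), visit time (1, 3, 6, and 12 months), and treatment pathway-by-visit time interaction", estimated by restricted maximum likelihood. The result is read off as follows: "Primary treatment comparisons will be contrasts in least squares means between treatment groups at the endpoint visit". Other outcomes follow the same plan: "The CGI scores and SCID diagnoses will be analysed in a similar fashion", and Aim 2 applies the same approach to SF-12, EQ-5D and PDSQ.

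On allocation, Randomization states: "We will stratify the participants by the diagnosis of panic attack or panic disorder". Permuted blocks of 4 at 1:1 are used within each stratum.

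Table 2 (Participant timeline) marks PDSS, CGI, SCID, PDSQ, SF-12 and EQ-5D at baseline as well as at every follow-up visit. The only covariate adjustment mentioned anywhere is for ancillary treatments, under Participants & procedures.

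**The concern.** A baseline measure of the primary outcome and a stratification factor are the two covariates one expects first in the primary model of a stratified trial. Neither is named here, although both are known for every randomised participant. The promised adjustment for ancillary treatments does not replace them, because those are recorded at each time point and so include values after randomisation.

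The two omissions have different effects:

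- **Baseline PDSS.** Without it the standard error is valid, but larger than it needs to be. Any chance difference between arms in baseline severity stays in the estimate.
- **Stratum.** Blocking within strata makes the arms more alike than simple randomisation would. A model without the stratum does not credit this, so its standard error is too large and the nominal 5% test rejects less often than 5% under the null.

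For the SCID diagnosis of panic disorder, the stratum is in effect the baseline value of the outcome, so leaving it out is hardest to defend there.

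**Working it through.** **Inputs from the protocol article (Sample size).** d = 0.516; two-sided alpha 0.05; power 90%; 80 per arm after 25% attrition; 212 randomised.

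**Assumptions, because the documents give no figure.** Correlation r between baseline and follow-up PDSS: 0.3 to 0.6. Share R² of outcome variance explained by the stratum: 0.05 to 0.20. d is taken in SD units of the PDSS score.

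**1. Reproduce the plan's figure, with no covariates.**

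- n per arm = 2(1.960 + 1.282)² / 0.516² = 78.9, rounded up to 79.
- Power at 80 per arm = Φ(0.516 × √(80/2) − 1.960) = Φ(3.264 − 1.960) = 90.4%. The exact t test gives 90.0%.
- Attrition: 79/0.75 = 105.3, rounded up to 106 per arm, or 212 in total. Starting from 80 per arm gives 160/0.75 = 213.3, or 214. In the other direction, 212 × 0.75 = 159.

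The stated size reproduces as a plain two-sample comparison without adjustment.

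**2. Add baseline PDSS.** Residual variance is multiplied by 1 − r². Power at 80 per arm = Φ(3.264/√(1 − r²) − 1.960). Equivalent unadjusted n per arm = 80/(1 − r²). Confidence interval width is multiplied by √(1 − r²).

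| r | Variance factor | Power, 80 per arm | Equivalent n per arm | n per arm for 90% | Interval width |
|---|---|---|---|---|---|
| 0 | 1.00 | 90.4% | 80 | 79 | 1.00 |
| 0.3 | 0.91 | 92.8% | 88 | 72 | 0.95 |
| 0.5 | 0.75 | 96.5% | 107 | 60 | 0.87 |
| 0.6 | 0.64 | 98.3% | 125 | 51 | 0.80 |

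**3. Omit or include the stratum.** After stratified blocked allocation the true standard error is about √(1 − R²) times the one the unadjusted model reports.

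- Actual type I error without the stratum = 2[1 − Φ(1.960/√(1 − R²))].
- Power without the stratum = Φ((3.264 − 1.960)/√(1 − R²)).
- Power with the stratum = Φ(3.264/√(1 − R²) − 1.960), and type I error returns to 5%.

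| R² | Type I error, stratum omitted | Power, omitted | Power, included |
|---|---|---|---|
| 0.05 | 4.4% | 90.9% | 91.7% |
| 0.10 | 3.9% | 91.5% | 93.1% |
| 0.20 | 2.8% | 92.7% | 95.4% |

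The gains in steps 2 and 3 should not be added together. Diagnosis and baseline PDSS probably carry overlapping information.

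**The case against.** The strongest reply is that the article is a condensation and its list covers only categorical effects. Baseline PDSS is continuous, so its absence from that list does not prove exclusion. The list is also visibly incomplete, since the adjustment for ancillary treatments appears elsewhere. For baseline PDSS this has some force. It does not explain the stratum, which is categorical, is the randomisation factor, and belongs in just such a list. The article also goes beyond silence: it names the response visits, the model terms and the contrast.

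A second reply is that the plan is adequately powered as it stands and that every gain above rests on assumed values. Both statements are true. They limit the weight of the point without removing it, because the adjustment costs nothing.

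Three stronger readings are tempting and are not supported:

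- **That the model fails to analyse the change on which the trial was sized.** The sizing sentence reads "Sample size was estimated based on change in panic symptom severity with PDSS score at 1-month post-intervention as the primary outcome", which names both change and the score. Data analysis does not say whether the response is the raw score or change from baseline. Under randomisation both have the same expected difference between arms.
- **That dropout is ignorable only with baseline in the model.** This is too absolute. Dropout related to baseline does not by itself bias the arm contrast, and earlier observed visits carry part of the baseline information.
- **That a Gaussian model is fixed for the yes/no SCID diagnosis.** The reference to a similar analysis leaves room for a logistic model with the same terms.

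**Conclusion.** The point holds as a matter of efficiency and calibration, not of validity. The model as listed gives an unbiased comparison and does not inflate type I error, and the stated sample size is correct for it.

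What is lost depends on quantities the documents do not give. With a baseline-to-follow-up correlation of 0.3 to 0.6, leaving out baseline PDSS forgoes a 9% to 36% cut in residual variance, equivalent to analysing 88 to 125 per arm instead of 80, and power of about 93% to 98% instead of 90%. If the stratum explains 5% to 20% of outcome variance, omitting it lowers the actual size of the 5% test to about 4.4% to 2.8%. The absence of the stratum is clear from the text. The absence of baseline PDSS is a fair reading of it, but less certain. The change should be made, though the trial does not fail without it.

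**What to change.** In the primary model, add baseline PDSS, a baseline-by-visit interaction, and the panic attack/panic disorder stratum as fixed effects beside arm, visit and arm-by-visit. For CGI, SF-12, EQ-5D and PDSQ, use the same model with the matching baseline score. For the SCID panic disorder diagnosis, state the binary analogue, a logistic mixed model or GEE, with stratum, arm, visit and arm-by-visit.

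The cost is a sentence or two in the analysis plan, settled before any unblinded analysis. All covariates are already collected at baseline, and neither the sample size nor the visit schedule changes.

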## Methods and analysis

### Study design

This 12-month superiority trial will follow a two-stage parallel group multi-site RCT design. Screening will be done at the first stage, followed by baseline assessments and block randomization in a 1:1 ratio to either the screening alone (SCREEN) or stepped-care (STEP) arms at the second stage. Only patients with a confirmed diagnosis of panic-related anxiety will be randomized at stage two. Masked follow-up assessments will be conducted by an independent evaluator at 1, 3, 6, and 12 months (See Fig. 2). We will follow the Consolidated Standards of Reporting Trials (CONSORT) guidelines for designing and reporting of randomized parallel-group non-pharmacologic intervention trials [37–39]. The trial protocol follows the SPIRIT recommendations and has been registered at clinicaltrials.gov (NCT03632356, 15 August 2018, current protocol version 4.0 dated 21 February 2019).

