### Setting

The study will be conducted at multiple EDs in SingHealth, the largest public healthcare group in Singapore. Recruitment sites will include Singapore General Hospital (SGH), Changi General Hospital (CGH), and Sengkang General Hospital (SKH). All patients will be triaged based on severity using the Singapore Patient Acuity Category Scale [40]. Chest pain is the presenting complaint in up to 40% of triage level 1 and 2 cases (the most severe triage categories) [41].

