*Inclusion Criteria:* 1. Diagnosis of panic attack or panic disorder confirmed by the SCID interview 2. Willing to enter randomized trial	*Exclusion Criteria:* 1. Does not meet criteria for panic attack or panic disorder based on the SCID interview 2. Received CBT for panic symptoms in the last 12 months 3. Unwilling to enter randomized trial

In order to maximize generalizability to the broad group of patients with panic symptoms who present to the ED, we will not exclude patients who have received other types of psychotherapy for panic symptoms or those who are being treated with antidepressant medications. However, we will assess for these treatments at each time point and we will control for ancillary treatments in subsequent analyses. Patients who have received CBT for panic symptoms in the prior 12 months will be excluded.

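### The stated mixed model omits the diagnosis stratum used in randomisation, and hospital, so precision is given up and the test may be mildly conservative

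*Protocol article*

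**What the plan says.** Under Study design, the protocol article describes the trial this way: "This 12-month superiority trial will follow a two-stage parallel group multi-site RCT design". Under Setting it names three hospitals: "Recruitment sites will include Singapore General Hospital (SGH), Changi General Hospital (CGH), and Sengkang General Hospital (SKH").

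Under Randomization, the allocation code is "contained within sequential sealed envelopes". The one declared stratification factor is diagnosis: "We will stratify the participants by the diagnosis of panic attack or panic disorder". Blocking follows: "Within each stratum, we will apply a permuted block randomization scheme with a block size of 4 and a 1:1 randomization ratio". Hospitals come up in that section only in a sentence on timing: "The randomization block will be generated before commencing the study at the various sites". It does not say whether there is one envelope sequence for the trial or one per hospital.

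Under Data analysis, Aim 1, the primary model is given as the "fixed categorical effects of treatment pathway (STEP, SCREEN), visit time (1, 3, 6, and 12 months), and treatment pathway-by-visit time interaction", fitted by restricted maximum likelihood. The primary comparison is the contrast in least squares means at the endpoint visit. The CGI scores and SCID diagnoses are to be handled in a similar way, and Aim 2 carries the approach over to the SF-12, EQ-5D and PDSQ.

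The only other adjustment mentioned is under Participants & procedures: "we will control for ancillary treatments in subsequent analyses". That covers neither diagnosis nor hospital.

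**The concern.** The article states both how patients are allocated and which effects the model contains, and the two do not match. Diagnosis is fixed as a design factor and then drops out of the analysis. Whether a patient has isolated panic attacks or panic disorder is plausibly prognostic for a panic severity score, so this is the firmer half of the point. Hospital is the second half: it is a recognised feature of the design, and depending on the envelope layout it may also be a blocking factor.

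Blocking within a factor forces the arms to be nearly balanced on it, so that factor contributes little to the true sampling variation of the treatment difference. A model without the factor still counts its variance as residual error. The standard error is then too large and the test rejects less often than its nominal level. If a prognostic factor is not blocked on, its variance is a real part of the sampling error, and adjustment removes most of it. In both cases what is at stake is precision, not validity.

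**Working it through.** **1. The plan's own figure.** Inputs from Sample size: standardised difference 0.516, two-sided 0.05, power 90%, 80 evaluable per arm, 25% attrition, 212 randomised.

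- Normal approximation: 2 × (1.960 + 1.282)² / 0.516² = 78.9, so 79 per arm.
- Noncentral t with 80 per arm: noncentrality 0.516 × √(80/2) = 3.263, power 0.900.
- Attrition: 79/0.75 = 105.3, so 106 per arm and 212 in total. From 80 per arm, 107 and 214.

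The stated sample size reproduces, and 0.900 is the reference power below.

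**2. Gain from adjusting for hospital.** Let ρ be the share of PDSS variance between hospitals. The article gives no value, so ρ is an assumption. Taking 0.516 on the total SD, the adjusted standard error is √(1 − ρ) times the unadjusted one, and the effective standardised difference is 0.516/√(1 − ρ).

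| ρ (assumed) | SE factor √(1 − ρ) | 0.516/√(1 − ρ) | Power, 80 per arm |
|---|---|---|---|
| 0 | 1.000 | 0.516 | 0.900 |
| 0.01 | 0.995 | 0.519 | 0.903 |
| 0.02 | 0.990 | 0.521 | 0.906 |
| 0.05 | 0.975 | 0.529 | 0.914 |
| 0.10 | 0.949 | 0.544 | 0.928 |

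So 1–5% of variance shortens the standard error by 0.5–2.5%. In patients that is 212 × [1/(1 − ρ) − 1], or about 2 to 11. If 0.516 was instead meant on the within-hospital SD, power without hospital in the model is 0.897 at ρ = 0.01, 0.885 at 0.05 and 0.868 at 0.10.

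**3. Type I error when a blocked factor is left out.** With near-perfect balance on the factor, the test statistic under the null has SD of about √(1 − ρ), so the actual level is about 2 × [1 − Φ(1.960/√(1 − ρ))]. This gives 0.049 at ρ = 0.01, 0.044 at 0.05 and 0.039 at 0.10. The formula applies to diagnosis with its own variance share, which the article does not give either, and to hospital if envelopes are blocked by hospital.

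**4. Simulation.** Setup: 212 patients, 25% dropout, blocks of 4 within diagnosis, three hospitals with assumed shares of 50/30/20%, 6,000 runs per scenario, analysed at a single visit by linear regression. Monte Carlo error on a 5% rate is √(0.05 × 0.95/6000) = 0.003. Diagnosis was given no effect on outcome, so the runs speak to hospital only.

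- One sequence across hospitals, hospital not in the model: type I error 0.045–0.052; mean estimate 0.514–0.517 against a true 0.516.
- Envelopes blocked by hospital, hospital not in the model: type I error 0.042 at ρ = 0.05 and 0.038 at ρ = 0.10, in line with step 3.
- Adding hospital raised power by about 1 point at ρ = 0.05 and by 2 to 3 points at ρ = 0.10.
- The largest between-arm difference in any hospital's share of evaluable patients had a 95th percentile of about 17 percentage points with one sequence and about 9 with blocking by hospital.

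**The case against.** The strongest reply is that this is a condensed article and that a statistical analysis plan may add covariates. The Data analysis section does not call its list of effects exhaustive, and the promise elsewhere to control for ancillary treatments shows that other terms may enter. This stands in part: the article does not exclude adjustment, and a fuller plan could already contain it. It does not dispose of the point. The article names its stratification factor and its model effects explicitly, and the model as stated does not include that factor.

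A second reply is that nothing stated is invalid. That stands fully. A reader might infer that hospital differences bias the treatment contrast or inflate false positives. The documents do not support this: patients are randomised individually, the unadjusted contrast is unbiased on average, and type I error is at or below nominal. Chance imbalance between hospitals under one shared sequence is already reflected in the unadjusted standard error.

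Three further inferences should be resisted:

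- **Layout.** One might assume that each hospital holds its own blocks, or that nothing balances the arms within a hospital. The article settles neither. If one sequence were handed out in consecutive batches, most blocks would stay whole within a hospital.
- **Imbalance.** Treating allocation as coin tosses gives an SD of √(0.25/50) = 7 points for the STEP share at a hypothetical 50-patient hospital. That ignores the 1:1 blocking; for 50 drawn from 212 near-balanced allocations it is 0.071 × √(162/211) = 0.062, about 6 points.
- **Assessors.** Follow-up raters are described as independent or masked but are not tied to hospitals, and telephone follow-up is allowed. Rater differences between hospitals are therefore not documented. All three hospitals also belong to one healthcare group, which may keep differences small.

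**Conclusion.** The point holds as a cheap improvement, not as a flaw that threatens the result. The stated model omits the declared stratification factor, and it omits hospital in a three-hospital trial. For diagnosis, and for hospital if it is blocked on, the consequence is a standard error that is somewhat too large and a mildly conservative test. If one sequence is shared, omitting hospital costs only a little precision.

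For hospital, an assumed 1–5% variance share means a standard error 0.5–2.5% shorter and power of 0.903–0.914 instead of 0.900. These figures rest on the assumed share, on 0.516 referring to the total SD, and on a single-visit approximation to the repeated-measures model. No size can be given for diagnosis, because the article reports no variance share for it.

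**What to change.** Add the diagnosis stratum (1 degree of freedom) and hospital (2 degrees of freedom) as fixed effects in the mixed models for PDSS, CGI, SF-12, EQ-5D and PDSQ, and in the model for SCID diagnosis. State in one sentence whether the envelopes form a single sequence or one per hospital. Settle both before outcome data are compared by arm, so that adjustment cannot become a data-driven choice.

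The cost is three degrees of freedom, which leaves power at 80 per arm unchanged to three decimals, plus a line or two of text. No new data are needed. The one real consequence is for SCID diagnosis: on a logistic scale the odds ratio becomes conditional on diagnosis stratum and hospital, and the plan should say so. Leave the randomisation and the sample size as they are.

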### Criteria for ‘stepping up’ in the stepped-care intervention arm

The decision to step-up interventions for patients in the STEP arm will be guided by remission status as assessed by the PDSS and CGI. Acute remission status is defined by a CGI score of 1 or 2 (no disorder or borderline disorder) and no panic attacks for a one-week period. Full remission is defined by maintenance of this status for two consecutive months [49]. Participants who show acute remission of panic symptoms one month after completing the psychoeducation session will enter the follow-up phase. Those who do not show acute remission of panic symptoms at one-month post-psychoeducation or return to the ED with panic symptoms within three months will be stepped up to receive the 5-session CBT protocol.

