### Participant timeline

Participants in both arms will be involved in the trial for a period of 12 months. Following recruitment at baseline at the ED, masked follow-up assessments will be conducted by an independent interviewer at 1, 3, 6, and 12 months. The timeline of study assessments is shown in Table 2. Participants in the STEP arm will receive psychoeducation within 1 week of discharge from the ED and those who are stepped-up will receive 5 weekly sessions of CBT between the 1-month and 3-month follow-up.

**Table 2 Tab2:** Timeline of study assessments

Construct	Outcome Measure	Time point					
		Screening	Baseline	1 month	3 months	6 months	12 months
Panic Screening	CDR^a^	x					
Panic Attack/Disorder Diagnosis	SCID Panic Module^a^		x	x	x	x	x
Panic Symptom Severity	PDSS^a^		x	x	x	x	x
	CGI^a^		x	x	x	x	x
Psychiatric Comorbidity	PDSQ^b^		x	x	x	x	x
Health-Related Quality of Life	SF-12^b^		x	x	x	x	x
Healthcare Utilization	Electronic medical record						x
Direct Healthcare Costs	Electronic billing data						x
Cost Effectiveness	SF-6D/EQ-5D^b^		x	x	x	x	x

^a^Clinician-rated outcomes. ^b^Patient-reported outcomes

*CDR* Clinical Decision Rule; *SCID5 RV* Structured Clinical Interview for DSM-5; *PDSS* Panic Disorder Severity Scale; *CGI* Clinical Global Impressions Severity Scale; *PDSQ* Psychiatric Diagnostic Screening Questionnaire; *SF-12* Short Form Health Survey; *EQ-5D* EuroQoL- 5 Dimension

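### The 90% power is calculated for PDSS at 1 month after the intervention, but the primary test is at the endpoint visit, and Aim 1 adds CGI to the primary outcome

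*Protocol article*

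**What the plan says.** Three sections of the protocol article bear on which comparison decides Aim 1.

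- **Sample size:** "Sample size was estimated based on change in panic symptom severity with PDSS score at 1-month post-intervention as the primary outcome". The paragraph cites large pre-to-post effects for the CBT protocol, then expects a smaller one for psychoeducation by itself, and assumes d = 0.516. It gives 80 per group after 25% attrition, 90% power, two-sided 0.05 and 212 randomised.
- **Data analysis, Aim 1:** a mixed model with visits at 1, 3, 6 and 12 months and tests at two-sided 0.05. Then: "Primary treatment comparisons will be contrasts in least squares means between treatment groups at the endpoint visit". The endpoint visit is not given a month. The section refers to one primary outcome variable and adds: "The CGI scores and SCID diagnoses will be analysed in a similar fashion".
- **Specific aims:** "The primary outcome under Aim 1 will be clinician-rated severity of panic symptoms, measured using the Panic Disorder Severity Scale (PDSS", and the same sentence continues "and the Clinical Global Impression Scale (CGI".

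Two further sections fix the timing. Study design describes a 12-month superiority trial. Participant timeline says that "those who are stepped-up will receive 5 weekly sessions of CBT between the 1-month and 3-month follow-up".

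**The concern.** The sample size and the primary test refer to different visits, and the difference is one of substance. At 1 month the STEP arm has had one psychoeducation session and no CBT. By month 12 it has had the whole stepped-care sequence. Aim 1 asks about stepped care, so the endpoint contrast answers it and the 1-month contrast does not. The power statement, with the effect size behind it, belongs to the one that does not.

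Two things are at stake. The trial has no stated power for the contrast that decides it. And a positive 1-month PDSS result could be presented as the primary finding, with the Sample size section as support, although it would show only what psychoeducation does.

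The lesser issue is the scale. Specific aims puts CGI beside PDSS as a measure of the primary outcome, and no rule says whether one or both must succeed.

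**Working it through.** **Inputs from the protocol article.** d = 0.516, two-sided alpha 0.05, power 90%, 80 evaluable per group, 25% attrition, 212 randomised (Sample size); 1:1 allocation (Randomization).

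**1. Reproduce the stated size.** Normal approximation, per arm:

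n = 2 × (1.960 + 1.282)² / 0.516² = 2 × 10.51 / 0.2663 ≈ 78.9, so 79.

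The two-sample t-test gives 79.9, so 80, as stated. Power at 80 per arm is 0.900. Inflating for attrition, 79/0.75 = 105.3, so 106 per arm and 212 in all; 80/0.75 = 106.7, so 107 per arm and 214 in all. The plan's figures are sound for the contrast they describe.

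**2. Can the two visits be reconciled?**

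- *The endpoint visit means month 1.* The conflict goes, but the primary test then precedes all CBT and does not test stepped care.
- *One month post-intervention means one month after CBT.* That is still not month 12, and SCREEN participants, like STEP participants who are not stepped up, have no CBT from which to count.
- *The endpoint visit means month 12.* This fits the 12-month design and the model, but then the sample size rests on another visit and on one component of the intervention.

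No reading makes the two sections agree while still testing stepped care.

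**3. Power at the endpoint visit.** The document gives no effect size for it, so the effects below are assumptions. Power ≈ Φ(d × √(80/2) − 1.960); the table gives the t-test values.

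| Assumed d at endpoint | d × √40 | Power, 80 per arm |
|---|---|---|
| 0.30 | 1.90 | 47% |
| 0.40 | 2.53 | 71% |
| 0.45 | 2.85 | 81% |
| 0.516 | 3.26 | 90% |
| 0.60 | 3.79 | 96.5% |
| 0.70 | 4.43 | 99% |

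Attrition has a smaller influence. With d held at 0.516 and 106 randomised per arm, power is 90% at 25% attrition, 88% at 30%, 85% at 35% and 82% at 40%. Rates above 25% are assumptions.

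**4. Two scales.** If success on either PDSS or CGI at 0.05 sufficed, type I error would be 1 − P(|Z₁| < 1.96 and |Z₂| < 1.96) for two standard normal statistics with correlation r. The document gives no r, so it is assumed.

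| Assumed r | Type I error |
|---|---|
| 0 | 9.75% |
| 0.6 | 8.75% |
| 0.7 | 8.35% |
| 0.8 | 7.8% |

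If both had to succeed, alpha would not be inflated. With d = 0.516 on each scale, power would be 84.5% to 86% for r of 0.6 to 0.8. If PDSS alone decides, alpha is 5%.

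**The case against.** Four points can be made for the plan.

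*The significance level is in order.* A reader might infer that the 5% level has come loose from the primary test as the power has. It has not: Data analysis sets two-sided 0.05 and in the next sentence places the primary comparison at the endpoint visit. This stands. Only the power is detached.

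*There is no licence to succeed at any visit.* A reader might count every visit and scale as a separate chance of success and arrive at a much larger error rate. The text does not support that. Data analysis names one visit for primary comparisons, nothing makes the 3- or 6-month contrasts primary, and the Sample size section is a basis for sizing, not a second success rule. This stands too.

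*PDSS is effectively the sole primary scale.* Sample size names PDSS alone, and Data analysis has one primary outcome variable with CGI handled separately. This largely stands. The scale issue is loose wording in the aims and weaker than the visit conflict, but it should be closed.

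*The endpoint effect may be larger than 0.516.* The plan treats psychoeducation as the more modest component, and stepped-up participants will have had CBT by then. This also stands. A reader might infer that the trial is underpowered, and the documents do not show that. Equally, nothing in them shows that the effect persists to month 12.

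None of these points reconciles the two visits.

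**Conclusion.** The concern holds as an inconsistency in the visit, with a secondary ambiguity in the scale. The stated 90% power is correctly calculated for PDSS at 1 month post-intervention, with an effect argued from psychoeducation alone, and it is not attached to the endpoint contrast that decides Aim 1. It carries over only if the effect there is also 0.516 SD and attrition is no worse than 25%; the protocol article argues neither for that visit. Endpoint power is therefore unknown, from about 47% to 96.5% for assumed effects of 0.30 to 0.60.

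The alpha consequence is conditional. Type I error is about 8–9%, at assumed correlations of 0.6–0.8, only if CGI alone could also decide Aim 1. Specific aims leaves that open, while the other two sections lean against it.

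The power figures rest on a simple two-sample comparison with 80 evaluable per arm. The planned mixed model may do somewhat better with incomplete follow-up, but that does not supply the missing endpoint effect size.

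**What to change.** Change Specific aims, Sample size and Data analysis together, before unblinding.

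1. Name one primary outcome: PDSS at one stated visit, tested as the model contrast at two-sided 0.05. Month 12 fits the Study design and Data analysis sections; the sponsor should confirm it. Replace the undefined endpoint visit with that month.
2. Make CGI, SCID diagnosis and the other visits secondary. Report 1-month PDSS as the effect of psychoeducation alone.
3. Restate the power for the chosen visit, with an effect size and an attrition rate justified for it, and show power over a range of effects as in the table above. Moving d = 0.516 to month 12 without a reason specific to that visit would repeat the fault.

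The cost is a protocol amendment while recruitment is under way (Study status), with the registration brought into line. The power statement may become less favourable. Whether 212 remains enough cannot be said until the endpoint effect is justified.
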